### Participant timeline

The trial will be conducted over a period of 3 years in 4 phases. During the phase 1, with duration of 8 months, 175 farmers will be recruited to assess their baseline knowledge, attitudes, and practices (KAP) regarding pesticide usage, which will be correlated with quality-of-life and biochemical parameters.

In the phase 2, which will last 4 months, around 20 to 30 farmers will participate in qualitative interviews to share their needs and perspectives on pesticide usage patterns, disposal methods, and storage practices. Additionally, 10 to 20 key stakeholders, including pesticide dealers, scientists from Farm Science Centre [Krishi Vigyan Kendra’s (KVK’s)], joint directors of agriculture, assistant director of agriculture, subject matter specialist [SMS] will be involved from the selected villages across different districts, to gather qualitative insights and recommendations regarding pesticide usage patterns.

Following this, phase 3 will be conducted over 6 months, which focuses on the development and validation of the educational module. This phase will be followed by a pilot implementation lasting further 6 months.

The final phase 4 will be executed as a randomized controlled trial (RCT), where the validated educational module will be implemented in the selected villages for a specific duration of 2 months. Participants will be followed up at intervals of 6 months and 12 months. The total duration of phase 4 will be 1 year.

### Sample size

The sample size for each phase of the study was calculated distinctly, tailored to the study design and objectives. A formal power calculation was conducted to ensure appropriate statistical power for detecting meaningful differences.

For phase 1, the sample size was determined using data from Sam KG et al. (2007) [31], a study conducted in Udupi, Karnataka, India, which reported a baseline Knowledge, Attitude, and Practice (KAP) score of 30.88 with a standard deviation of 10.33. The required sample size was calculated using the following formula for comparing two means:

$$\mathrm{n}\;= \;2\times\;[(\mathrm{Z}_{\alpha/2}\;+\;\mathrm{Z}_{\beta})\;/\;\mathrm{Z}_{\delta}\;]^{2}$$ where, n = required sample size per group, Z_α/2_
**=** standard normal deviate for a given significance level (e.g., 1.96 for 5% significance level), Z_β_ = standard normal deviate for the desired power (e.g., 0.84 for 80% power), σ = standard deviation of the outcome variable (10.33 from prior study) and Z_δ_ = expected mean difference in the effect size.

A statistical power of 80% was chosen, which is widely considered an acceptable standard in health and social science research [40]. A power of 80% indicates that there is an 80% probability of detecting a true effect if one exists, while maintaining a Type I error (α) of 5%. Accounting for a 10% dropout rate, a total of 175 farmers will be selected using the stratified sampling method for the KAP assessment, quality of life evaluation, and laboratory investigations.

In phase 2, with approximately 20-30 farmers and 10–20 stakeholders from various villages across the selected 3 districts will be involved in the qualitative interviews for the need assessment phase.

Phase 3 focuses on the development and validation of the educational intervention by 6 experts from various domains including experts from agricultural sciences, pharmacy practice, community medicine, public health, and emergency medicine.

For Phase 4, the sample size was determined based on findings from a pilot study involving 12 farmers, with equal allocation to intervention and control groups in a simple randomized controlled trial (RCT) design. The final sample size was calculated using the power calculation formula for a paired t-test:$$\mathrm{n}\;=\;2\times\;[(\mathrm{Z}_{\alpha/2}\;+\;\mathrm{Z}_{\beta})^{2}\;*\;2\sigma^{2}\;/\;\mathrm{Z}_{\delta}\:^{2}]$$, where, n = required sample size per group, Z_α/2_**=** standard normal deviate for a given significance level (e.g., 1.96 for 5% significance level), Z_β_ = standard normal deviate for the desired power (e.g., 0.84 for 80% power), σ = standard deviation of the outcome variable (10.33 from prior study) and Z_δ_ = expected mean difference in the effect size.

To ensure the effective implementation of the educational intervention, farmers will be stratified by age and education level.

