### Trial design

This study adopts a multi-phase, mixed-methods approach to address pesticide safety practices among farmers in Karnataka state. The study will be conducted in 4 different phases. Phase 1 is an analytical cross-sectional study, designed to evaluate the baseline knowledge, attitudes, and practices (KAP) of farmers using structured questionnaires. Phase 2 involves qualitative face-to-face interviews to gain deeper insights into the behavioural and contextual factors influencing pesticide usage and safety practices.

Phase 3 involves development and validation of need-based education module, where selection of experts will be carried out by purposive sampling technique. Phase 4 is a multicentric RCT, where 3 districts that includes 6 villages will be selected based on randomization. This study will be conducted as a two-arm, single-blind, parallel group with simple randomization of the districts and cluster randomization of farmers. The allocation ratio is 1:1, with one arm receiving the educational intervention and the other serving as a control group with no intervention. The outcomes will be assessed in terms of mean difference with the pre and post assessment in terms of KAP. The trial adopts a superiority framework [33] to assess the effectiveness of the educational intervention in improving pesticide safety knowledge, attitudes, and practices among farmers.

The below Fig. 1 depicts the trial process from recruitment to randomisation.

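### Phase 1's 175 farmers are justified by 80% power from a two-group comparison of means, but no two-group contrast is named for Phase 1, which describes and correlates KAP in one sample

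*Protocol article*

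**What the plan says.** The *Sample size* section of the protocol article opens by asserting that each phase was sized separately to suit its own design and aims. For Phase 1 it takes from an earlier study in Udupi a KAP "score of 30.88 with a standard deviation of 10.33". It then says: "The required sample size was calculated using the following formula for comparing two means". The legend gives "n = required sample size per group", lists σ = 10.33, and describes the denominator as the "expected mean difference in the effect size", with no number. The section adds that "A statistical power of 80% was chosen" together with a 5% type I error, allows for 10% dropout, and states a single total of 175 farmers.

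Elsewhere the article describes the phase differently. *Trial design*: "Phase 1 is an analytical cross-sectional study, designed to evaluate the baseline knowledge, attitudes, and practices (KAP) of farmers". *Participant timeline* says of the Phase 1 KAP assessment: "which will be correlated with quality-of-life and biochemical parameters". The first item under *Objectives* is the same: assess KAP and correlate it with quality of life and biochemical parameters. *Recruitment of participants* takes equal numbers from three districts and plans no comparison between them.

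**The concern.** A two-means formula answers one question: how many per group are needed to detect a given difference between two groups. Phase 1, as the article describes it, has one group, and its aims are description and correlation. The 80% power therefore attaches to a contrast that the article does not name for this phase, which conflicts with its own statement that each size suits its phase. Supplying the missing difference would not cure this, because the formula would still be for two groups.

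At stake is what a reader can take from the number. Phase 1 feeds the content of the educational module. A reader who sees 80% power will assume that it applies to the correlations, and the article gives no means of knowing how small a correlation 175 farmers could detect or how precisely mean KAP would be known.

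**Working it through.** **Inputs (all from *Sample size*).** Two-sided alpha 5% (Z = 1.96); power 80% (Z = 0.84), so the sum is 2.80; SD 10.33; mean 30.88; 10% loss; total 175. The mean difference is not stated.

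**Step 1: the printed formula.** It reads n = 2 × [(Zα/2 + Zβ)/Zδ]² per group. σ is listed in the legend but does not appear in the expression. The formula is valid if Zδ is a standardised difference d, and σ then plays no part in it. For a difference Δ in KAP points, the equivalent is n = 2 × (2.80 × 10.33/Δ)².

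**Step 2: trying to reproduce 175.** With no difference stated, one can only solve backwards, and three readings fit:

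| Reading of 175 | Implied difference | Check |
|---|---|---|
| Total of two groups, after 10% loss | about 4.6 points (d about 0.45) | 2 × (2.80 × 10.33/4.6)² = 79.1 per group; about 158 in total; 158/0.9 = 176 |
| Per group, after 10% loss | about 3.25 points | 2 × (2.80 × 10.33/3.25)² = 158.4, so 159; 159/0.9 = 177 (159 × 1.1 = 175) |
| Per group, before loss | d = 0.3 | 2 × (2.80/0.3)² = 174.2, so 175 |

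The first is sensitive to rounding: at exactly 4.6 points, rounding up gives 80 per group and 160/0.9 = 178. The figure of 175 can be neither confirmed nor refuted, and none of the three differences belongs to a contrast named for Phase 1.

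**Step 3: is there a natural pair of groups?** The only structural grouping is three equal districts of about 175/3 = 58. Comparing two of them with 80% power would detect 2.80 × 10.33 × √(2/58) = 5.4 points, which is none of the values above. No such comparison is planned.

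**Step 4: what 175 gives for the stated aims.** After 10% loss, 175 × 0.9 = 157.5, so take 157.

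- Smallest correlation detectable with 80% power (Fisher z), r = tanh(2.80/√(n − 3)): n = 175 gives tanh(2.80/√172) = 0.21; n = 157 gives tanh(2.80/√154) = 0.22.
- Power for assumed correlations, n = 157 to 175: r = 0.1, 24% to 26%; r = 0.2, 71% to 76%; r = 0.3, 97% to 98%.
- 95% half-width for mean KAP, 1.96 × 10.33/√n: n = 175 gives 1.53 points; n = 157 gives 1.62 points.

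The correlation figures are for one test without adjustment for multiplicity. The half-widths assume simple random sampling.

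**The case against.** The strongest reply is that the article is a condensed account. *Statistical analysis* lists no quantitative Phase 1 test at all, not even the correlation, so the Phase 1 analyses may sit in a fuller document. The phase is called analytical, the sampling is called stratified in *Sample size*, and equal numbers come from three districts; a comparison of KAP between strata is compatible with all of that. This part stands. A reader might infer that the power statement is false of every analysis planned for Phase 1, but the document does not support that. It supports only that the power matches no analysis named there. Since the article does name the aim, and names it as correlation, the mismatch remains on its face.

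A reader might also infer that the formula is wrong as printed, because a difference in KAP points in the denominator gives an absurdly small n. That does not follow either. The expression is the standard one for a standardised difference, and the legend's unclear wording can be read that way. What remains is a leftover σ in the legend and no stated value.

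Finally, it can fairly be said that 175 may be quite enough. Nothing here shows otherwise.

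**Conclusion.** The point holds in a limited form. The justification printed for Phase 1 is for a two-group comparison that the article does not name for that phase, and the 80% power should not be read as applying to the correlations or to the estimate of mean KAP. The number 175 cannot be reproduced, because three different readings fit it.

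The size of the problem is modest. Phase 1 is a survey ahead of the randomised phase, which has its own sample size paragraph. For the stated aims 175 farmers are of reasonable use: a single correlation of about 0.21 to 0.22 is detectable with 80% power, while one of 0.1 would be detected only about a quarter of the time. No document says which correlation matters, so neither adequacy nor inadequacy is shown. A reader might take 4.6 points as the planned difference; it is only one of the back-solved values.

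The figures rest on the quoted SD, a 10% loss, one unadjusted test and, for the precision of the mean, a sample that behaves as random. The last is doubtful: *Sample size* says the sampling is stratified, while *Recruitment of participants* says purposive.

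**What to change.** Keep 175. Replace the two-means formula and its power statement with one that matches the stated aim, for example:

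> 175 farmers (about 157 evaluable after 10% incomplete data) give 80% power at two-sided 5% to detect a single correlation of about 0.22 or more, unadjusted for multiple correlations. Mean KAP would be estimated within about ±1.6 points (SD 10.33) if the sample behaves as a simple random sample.

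If a comparison of two groups was intended, name the groups, state the difference in points or SD units, say whether 175 is a total or per group, and either use σ in the formula or drop it from the legend. In either case, reconcile stratified with purposive sampling, since the precision statement depends on it.

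The cost is one rewritten paragraph and one consistent description of the sampling. Enrolment does not change.

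### The Phase 4 sample-size formula is neither the paired formula it is called nor the per-group two-arm formula, and it ignores cluster allocation, so 80% power between arms is not demonstrated

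*Protocol article*

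**What the plan says.** All of this is in the protocol article.

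- **Sample size, Phase 4.** The size is said to rest on a pilot of 12 farmers, "with equal allocation to intervention and control groups in a simple randomized controlled trial (RCT) design". Then: "The final sample size was calculated using the power calculation formula for a paired t-test". The printed expression is n = 2 × [(Zα/2 + Zβ)² × 2σ² / δ²], where n is the "required sample size per group" and σ is the "standard deviation of the outcome variable (10.33 from prior study"). The Phase 1 text just above identifies 10.33 as the SD of a baseline KAP score in an earlier Udupi survey. Significance level and power enter only as examples, the latter as "standard normal deviate for the desired power (e.g., 0.84 for 80% power"). The Phase 4 text gives no value for δ and no resulting N.
- **Trial design.** Two arms, 1:1, superiority, three districts containing six villages, with cluster randomisation.
- **Random sequence generation and randomization.** Villages are allocated to the arms.
- **Recruitment of participants, Phase 4.** Districts are allocated to the arms.
- **Statistical analysis.** Paired t-tests compare results before and after the intervention.

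**The concern.** The sample-size calculation should match the question, the test and the unit of randomisation. Here the question is a difference between two arms and the unit is a village or a district. The formula carries the name of a within-person test, takes the SD of a single score, and treats farmers as independent.

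Two things are at stake. First, a reader cannot tell whether the expression gives farmers per arm or in total, which is a twofold difference in enrolment. Second, with so few clusters, between-village variation and the small degrees of freedom govern power far more than the number of farmers does. Neither enters the calculation.

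**Working it through.** **Inputs from the article:** σ = 10.33 (σ² = 106.71); z = 1.96 + 0.84 = 2.80, z² = 7.84; six villages, 1:1, hence three per arm if villages are the unit. **Assumed, because none is given:** δ (5 points as the main case), ICC, and baseline–outcome correlation r. There is no Phase 4 N to reproduce.

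**1. What the printed expression is.** 2 × z² × 2σ²/δ² = 4z²σ²/δ². At δ = 5:

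| Formula | Expression | Result |
|---|---|---|
| As printed, labelled per group | 4z²σ²/δ² | 4 × 7.84 × 106.71/25 = 133.9, so 134 |
| Two-arm comparison, per group | 2z²σ²/δ² | 66.9 |
| Two-arm comparison, total | 4z²σ²/δ² | 133.9 |
| Paired, number of pairs, r = 0.5 | z² × 2σ²(1−r)/δ² | 33.5 |

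The ratio of printed to two-arm per-group size is 2 at any δ. The printed expression is four times the paired size at r = 0.5 and twice it at r = 0. It also equals the per-group size for a two-arm comparison of change scores if r = 0.

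**2. Power with independent farmers.** If 134 is per arm, SE = 10.33 × √(2/134) = 1.262 and δ/SE = 3.96. Power = Φ(3.96 − 1.96) = 97.7%. If 134 is the total (67 per arm), δ/SE = 2.80 and power is 80%.

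**3. Power with three villages per arm.** Design effect DE = 1 + (m − 1) × ICC, with m = 134/3 = 44.7 or 67/3 = 22.3. SE = 10.33 × √(2 × DE/n per arm). The test is a two-sided t on 6 − 2 = 4 df (critical value 2.776), with power from the noncentral t. No baseline adjustment; δ = 5.

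| ICC | DE, 134 per arm | Power, 134 per arm | Power, 67 per arm |
|---|---|---|---|
| 0 | 1.00 | 84% | 56% |
| 0.01 | 1.44 | 70% | 49% |
| 0.02 | 1.87 | 59% | 43% |
| 0.05 | 3.18 | 40% | 32% |

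Using normal quantiles instead of 4 df, 134 per arm gives 91%, 82% and 60% at ICC 0.01, 0.02 and 0.05.

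**4. How much clustering the doubling absorbs.** On 4 df, 80% power needs δ/SE = 3.76. The doubling supplies 3.96, so it tolerates a DE of (3.96/3.76)² ≈ 1.11. That is an ICC of 0.11/43.7 ≈ 0.003. With an assumed 87 per arm in villages of 29 and the 6.2 points for which the printed formula gives that size, the limit is about 0.004. It depends on village size: about 0.001 at δ = 3 (372 per arm) and 0.007 at δ = 8 (53 per arm).

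**5. Baseline adjustment.** Multiplying the variance by (1 − r²), 134 per arm at ICC 0.01 and 0.05 gives 81% and 50% at r = 0.5, and 93% and 65% at r = 0.7.

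**6. If districts are the unit.** Three districts in two arms leave one arm with a single cluster and 3 − 2 = 1 df. Power cannot then be meaningfully computed.

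**The case against.** The other side has several good points.

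- *A reader might infer that the trial is shown to miss a stated 80% power.* The article does not support that. The Phase 4 text gives no N or δ, and 80% appears there only as an example. The firm statement, "A statistical power of 80% was chosen, which is widely considered an acceptable standard in health and social science research", stands in the Phase 1 text. Only a lack of demonstration can be claimed.
- *A reader might infer that the formula is simply wrong for two arms.* It is the correct two-arm total, so one mistaken word, per group instead of total, would explain it. Taken literally it is conservative for independent farmers.
- *A reader might infer that 10.33 is the wrong SD.* It is unsuitable only against the paired label. A cross-sectional SD is the right kind for comparing scores between arms, and nothing shows 10.33 to be too large or too small. A pilot may supply one input and a prior survey another; the text does not say which came from where.
- *A reader might extend the criticism to Phase 1, where σ is defined but absent from the equation.* That formula is valid if its δ is a standardised effect, which the wording allows.
- The simple-RCT phrase may describe the pilot and not the Phase 4 assumption. The absence of any clustering term in the printed formula is the firmer evidence.
- This is a condensed article, and a full protocol may state δ, N and ICC. Their absence is not the point. The point is that what was printed does not fit the design printed beside it.
- Baseline adjustment removes the shortfall in some scenarios, for instance at ICC 0.01 with r = 0.5 or more.

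What remains is the mismatch of label and formula and the lack of any allowance for clustering. Neither is answered by these points.

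**Conclusion.** The concern holds in a limited form. The published Phase 4 calculation does not match the trial. Its paired label is contradicted by its expression, its per-group reading is double the two-arm size, and it ignores allocation by village or district. Power of 80% for the between-arm comparison is not demonstrated.

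A shortfall is likely but not proven. It rests on three villages per arm, a village-level analysis on 4 df, and assumed δ, ICC and r. On those terms, without baseline adjustment and with the literal (doubled) size, power drops below 80% once the ICC passes roughly 0.003 to 0.004 in the two main scenarios. If the printed expression is really the total, power on 4 df is about 56% even at ICC 0. With strong baseline adjustment and a small ICC, power can exceed 80%.

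**What to change.** 1. Reconcile four statements: the paired label against the printed expression; per group against total; the source of σ (pilot or prior survey); and the unit of randomisation (village in one section, district in another).
2. Replace the formula with a two-arm cluster calculation: n per arm = 2z²σ²(1 − r²)[1 + (m − 1) × ICC]/δ², with t quantiles on (clusters − 2) df in place of normal ones.
3. State δ with its justification on the KAP scale, the village size m, and N.
4. Show results over a range of ICC. Phase 1 data from the same villages can inform σ and the ICC, but only imprecisely, since the villages are few and the Recruitment section describes purposive selection.
5. Restate power or the detectable difference for the clusters actually randomised. As an illustration, with 134 per arm in three villages and no adjustment, the difference detectable with 80% power is 3.76 × SE: 5.7, 6.5 and 8.5 points at ICC 0.01, 0.02 and 0.05.

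The cost is a recalculation and a rewritten paragraph; no extra farmers are needed to correct the statement. The restated figures may be less favourable. If they are, and allocation has not yet happened, more villages will help more than more farmers. At δ = 5 and ICC 0.05, SE with three villages per arm cannot fall below 10.33 × √(2 × 0.05/3) = 1.89, so unadjusted power stays near 52% however many farmers are enrolled.

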### Recruitment of participants

The recruitment process will follow distinct approaches for each phase.

In phase 1, farmers will be recruited through purposive sampling method, utilizing suggestions from Farmer Producer Organizations (FPOs) and recommendations from District Agricultural Officers. Participants will be briefed on the study objectives, and informed consent will be obtained. Each participant will be provided with a Participant Information Sheet (PIS), which outlines the study’s purpose, procedures, potential risks, and benefits. Recruitment will proceed only after obtaining Institutional Ethics Committee (IEC) approval. Samples will be collected from 3 districts, with an equal number of participants from each district. The districts will be selected based on pesticide usage, crop types, pesticide poisoning exposure (intentional and accidental), farmers’ experience, education, and age. Eligible participants will be enrolled after meeting the inclusion criteria, completing baseline questionnaires, and undergoing laboratory investigations.

Phase 2 will involve qualitative interviews to assess farmers’ perceptions and needs, with consent obtained for audio recording of 20–30-minute sessions. Farmers from Phase 1, with substantial experience in pesticide spraying, knowledge of pesticide poisoning, and adequate educational qualifications, will be selected from the three districts to participate in the interviews. Stakeholders will include FPO heads, agricultural officers, and other community leaders involved directly or indirectly with the farmers in the pesticide handling and crop management.

In phase 3, for recruitment of the experts for the validation of the need-based educational module, experts will be selected by purposive sampling method based on their area of expertise. This includes experts from community medicine, public health, sociology, audio-visual section, agricultural officer and farmer representative. A focus group discussion will be carried out during the recruitment and interviews will be done to understand the needs of farmers based on opinions from experts. And finally, data from phase 1 and 2 along with expertise will be gathered to develop a need-based educational intervention.

In phase 4, the same villages from Phase 1 will be selected for recruitment. The districts will be randomized into control and intervention groups. Farmers will be identified using cluster sampling, with stratification based on age and agricultural experience. The intervention will be delivered to the experimental group at village halls or community centres. The cluster sampling approach ensures that participants are diverse in terms of age, educational level, and years of experience in agriculture allowing for a balanced representation across the groups.

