## Methods: Participants, interventions, and outcomes

### Patient and public involvement (PPI) – GRIPP2-SF

The study incorporates patient and public involvement (PPI) following the GRIPP2-SF (Guidance for Reporting Involvement of Patients and the Public – Short Form) [34], to ensure that the research is relevant, acceptable, and beneficial to the target population. Farmers will be involved to develop and validate the educational intervention based on their lived experiences with pesticide use. Farmers, agricultural officers, and community representatives will be engaged in the study, through focus group discussions to shape the study design, intervention content, and outcome measures. Their insights and experiences can help in the betterment of the mode of educational delivery and strategies to enhance adherence. During implementation, public representatives will be involved to support participant recruitment and provide feedback on intervention practicality. PPI members will also contribute to interpreting results, ensuring contextual relevance. Study findings will be disseminated through community meetings at village halls or community meetings. Reflections on PPI impact, including benefits and challenges, will be documented to develop future research.

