### Eligibility criteria

Inclusion criteria for study participants comprise: (a) Farmers who are actively engaged in regular pesticide spraying; (b) Farmers who are willing to provide informed consent (c) Farmers with a minimum of 5 years of experience in agriculture and pesticide spraying; (d) Farmers aged between 18 and 80 years, irrespective of their gender. Following this, any farmers who unwilling to provide consent and who are just involved in agriculture but lack pesticide spraying will be excluded from the study.

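### Phase 4 recruits in the Phase 1 villages without excluding farmers who helped build, validate or pilot the module, so farmers who already know its content can enter either arm

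*Protocol article*

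**What the plan says.** **Where Phase 4 recruits.** Under Recruitment of participants: "In phase 4, the same villages from Phase 1 will be selected for recruitment". Trial design puts the number of villages at six, across three districts.

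**Who works on the module beforehand.** The patient and public involvement section says "Farmers will be involved to develop and validate the educational intervention based on their lived experiences with pesticide use". It adds that farmers, officers and community representatives will be engaged "through focus group discussions to shape the study design, intervention content, and outcome measures". The Recruitment section lists among the validating experts "audio-visual section, agricultural officer and farmer representative". Participant timeline says of the development and validation phase: "This phase will be followed by a pilot implementation lasting further 6 months". The Sample size section mentions a pilot of 12 farmers, split equally between intervention and control.

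**Who is interviewed.** Phase 2 draws on "Farmers from Phase 1, with substantial experience in pesticide spraying, knowledge of pesticide poisoning, and adequate educational qualifications, will be selected from the three districts". According to Participant timeline, "around 20 to 30 farmers will participate in qualitative interviews to share their needs and perspectives on pesticide usage patterns, disposal methods, and storage practices".

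**Who is kept out.** Eligibility criteria give one list for the whole study. Apart from refusal of consent, the only exclusion is for farmers "who are just involved in agriculture but lack pesticide spraying will be excluded from the study". Taking part in an earlier phase is not mentioned.

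**The concern.** The comparator is no education, and the trial is framed as a superiority trial. Its contrast depends on the control farmers being unexposed to the module and on the intervention farmers meeting it for the first time. The plan returns to villages where the study has already worked, and it has no rule that separates the people who shaped or saw the module from those on whom it is tested.

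Two things are at stake. The first is a diluted treatment contrast, which costs power and understates the effect. The second is imbalance: with six villages, a handful of such farmers concentrated in one or two of them could be unevenly divided between the arms. Neither can be fully repaired in the analysis, so the matter belongs in the eligibility criteria before recruitment starts.

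**Working it through.** The plan has no figure of its own to reproduce here: it gives no final sample size for Phase 4 and no expected difference. The check is to set the sections side by side and then work out the direction of bias.

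**Step 1. Can the same farmers be eligible again?**
- Phase 1 farmers had to meet the inclusion criteria, and Phase 2 interviewees are Phase 1 farmers. They stay eligible for Phase 4 if they still spray, consent and are within the age limits.
- Interviewees come from all three districts. Whether villages are allocated (Random sequence generation) or districts (Recruitment), places that supplied interviewees can be in either arm.
- The focus-group, validation and pilot farmers have no stated villages. Nothing places them outside the Phase 4 villages.

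**Step 2. Do the existing safeguards cover this?**
- Study setting favours interior villages to limit contamination. That concerns influences from outside.
- Intervention asks participants to avoid other educational initiatives. That does not cover the study's own earlier phases.

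**Step 3. How strong is the prior exposure, by group?**

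| Group | Contact with the module | Number stated |
|---|---|---|
| Focus groups on content | Help shape it | None |
| Development and validation | See or judge it | Unclear: the Recruitment section names a farmer representative; the Sample size section lists six experts and no farmer field |
| Pilot | Intervention half receives it | 12, so 12/2 = 6 exposed, if this is the module pilot |
| Phase 2 interviews | State needs before the film exists | 20 to 30 |

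**Step 4. Direction of bias.** Let δ be the gain from the module, and let c_I and c_C be the shares of intervention and control farmers who already hold that gain when Phase 4 starts. Assume that they hold all of it and gain nothing further.
- *Change scores.* Mean change in the intervention arm is (1 − c_I)δ. A pre-exposed control has a raised baseline and changes by about zero, like any other control. Contrast = (1 − c_I)δ.
- *Post-intervention scores.* With μ the unexposed mean, the intervention arm is at μ + δ and the control arm at μ + c_C·δ. Contrast = (1 − c_C)δ.

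Each analysis carries one dilution factor. Trial design and Primary outcomes describe pre-post and mean change, so the first line is the one closer to the stated outcome.

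**Step 5. Scale.** For independent observations, holding power would multiply the sample size by 1/(1 − c)². Assumed shares, for scale only: c = 5% gives 1/0.95² = 1.11, and c = 10% gives 1/0.90² = 1.23. The documents do not allow c to be estimated, and clustering is ignored here.

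**The case against.** **Same villages are not the same farmers.** Phase 4 identifies farmers afresh by cluster sampling, so few or none of the earlier participants may be drawn. This stands: overlap is permitted, not planned.

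**The one group of any stated size, apart from the 12 pilot farmers, has the weakest mechanism.** A reader might divide the 20 to 30 interviewees by an assumed arm size and treat the result as the contaminated share of controls. The documents do not support that. The interviews last 20 to 30 minutes, collect needs and precede the film, and nobody is said to be taught anything. The Phase 4 denominator is not stated, and no expected contrast is given to which a dilution could be applied.

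**The two routes do not add up.** A reader might also infer that contaminated controls and a ceiling in the intervention arm both shrink the contrast. Step 4 shows that only one operates, depending on which scores are compared.

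**Repeat questionnaires.** Phase 1 farmers have already answered the KAP questionnaire, but both Phase 4 arms take it before the intervention anyway. That is a testing effect common to both arms.

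**The article is condensed.** A fuller protocol may hold Phase 4 exclusions. That is possible. However, the article itself states both the eligibility list and the return to the Phase 1 villages, and read together they allow the overlap.

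**Conclusion.** The gap is real and modest. As written, farmers who helped to develop, validate, discuss or pilot the module can be enrolled in either arm of Phase 4. The expected bias is toward no effect, so it threatens power and the size of the estimate rather than producing a false claim of superiority. Chance imbalance across six villages is a secondary risk and could act in either direction.

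No magnitude can be given. It would need the Phase 4 sample size, the numbers and villages of the focus-group and validation farmers, and the pilot sites. The conclusion rests on the criteria as printed and on the assumption that working on or seeing the module conveys at least part of its content.

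**What to change.** Add one Phase 4 exclusion: farmers who took part in focus groups on the module, its development, its validation or its pilot. As a precaution, extend it to the Phase 2 interviewees. Apply it identically in all villages, from a list fixed before allocation is known. State where the focus groups and the pilot take place, and reconcile the Recruitment and Sample size sections on whether a farmer is among the validators.

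The cost is a few dozen eligible farmers: 20 to 30 interviewees plus 12 pilot farmers is 32 to 42 if the groups do not overlap, plus the focus-group and validation farmers, whose number is not stated. Because interviewees are chosen for experience, knowledge and education, leaving them out also makes the Phase 4 sample slightly less experienced, equally by rule in both arms.

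Excluding people does not stop them talking to neighbours. Choosing Phase 4 villages not used in Phases 2 and 3 would go further, but at greater field cost. Recording Phase 1 participation is optional.
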